**8.4 Concomitant therapy**

All medication that the participant is taking at the time of enrolment will be recorded. Any changes or new medications added during the study will be recorded. The generic drug name, daily dose, route of administration, treatment start/stop date and indication will be recorded.

Participants will be asked to limit alcohol consumption and participants with Alcoholic Liver Disease advised to abstain completely.

Any drug, if considered necessary for the participant, is permitted at the discretion of the Investigator, with the following exceptions: Participation in another trial of an investigational product.

Of note, for patients with hepatitis, anti-viral treatment is allowed during the study. For patients with biliary obstruction, interventional drainage and cholagogue are allowed during the study.

**9. Adverse event reporting**

The collection and reporting of Adverse Events (AEs) will be in accordance with ICH GCP. Definitions of different types of AE are listed in Appendix 5. The Investigator should assess the seriousness and causality (relatedness) of all AEs experienced by the patient (this should be documented in the source data) with reference to the Investigator Brochure.

**9.1 Reporting requirements**

**9.1.1 Adverse events**

All medical occurrences which meet the definition of an AE (see Appendix 5 for definition) should be reported. Please note this includes abnormal laboratory findings.

**9.1.2 Serious adverse events**

Investigators should report AEs that meet the definition of an SAE (see Appendix 5 for definition).

**9.1.2.1 Events that do not require reporting on a Serious Adverse Event Form**

The following events should not be reported on an SAE Form:

• Hospitalizations for:

o Protocol defined treatment

o Pre-planned elective procedures unless the condition worsens

o Treatment for progression of the patient’s cancer

• Progression or death as a result of the patient’s cancer, as this information is captured elsewhere on the Case Report Form

**9.1.2.2 Monitoring pregnancies for potential Serious Adverse Events**

It is important to monitor the outcome of pregnancies of patients in order to provide SAE data on congenital anomalies or birth defects.

In the event that a patient or their partner becomes pregnant during the SAE reporting period please complete a Pregnancy Notification Form (providing the patient’s details) and return to the Trials Office as soon as possible. If it is the patient who is pregnant provide outcome data on a follow-up Pregnancy Notification Form. Where the patient’s partner is pregnant consent must first be obtained and the patient should be given a Release of Medical information form to give to their partner. If the partner is happy to provide information on the outcome of their pregnancy they should sign the Release of Medical information form. Once consent has been obtained provide details of the outcome of the pregnancy on a follow-up Pregnancy Notification Form. If appropriate also complete an SAE Form as detailed below.

**9.1.3 Reporting period**

Details of all AEs (except those listed above) will be documented and reported on entry into the trial until 28 days after the administration of the last treatment.

SAEs that are judged to be at least possibly related to trial treatment must still be reported in an expedited manner irrespective of how long after treatment administration the reaction occurred.

**9.2 Reporting procedure**

**9.2.1 Site**

**9.2.1.1 Adverse events**

AEs should be reported on an AE Form (and where applicable on an SAE Form). An AE Form should be completed at each visit and returned to the CORRECT Trials Office.

AEs will be reviewed using the Common Terminology Criteria for Adverse Events (CTCAE), version 5.0 (see Appendix 4). Any AEs experienced by the patient but not included in the CTCAE should be graded by an Investigator and recorded on the AE Form using a scale of (1) mild, (2) moderate or (3) severe. For each sign/symptom, the highest grade observed since the last visit should be recorded.

**9.2.1.2 Serious adverse events**

For more detailed instructions on SAE reporting refer to the SAE Form Completion Guidelines.

AEs defined as serious and which require reporting as an SAE (excluding events listed in Section 8.1 above) should be reported on an SAE Form. When completing the form, the Investigator will be asked to define the causality and the severity of the AE, which should be documented using the CTCAE version 5.0.

On becoming aware that a patient has experienced an SAE, the Investigator (or delegate) must complete, date and sign an SAE Form. The form should be faxed together with a SAE Fax Cover Sheet to the Trials Office using one of the numbers listed below as soon as possible and no later than 24 hours after first becoming aware of the event:

To report an SAE, fax the SAE Form with an SAE Fax Cover Sheet to:

[name]

On receipt the Trials Office will allocate each SAE a unique reference number. This number will be transcribed onto the SAE Fax Cover Sheet which will then be faxed back to the site as proof of receipt. If confirmation of receipt is not received within 1 working day please contact the Trials Office. The SAE reference number should be quoted on all correspondence and follow-up reports regarding the SAE. The SAE Fax Cover Sheet completed by the Trials Office should be filed with the SAE Form in the ISF.

For SAE Forms completed by someone other than the Investigator the Investigator will be required to countersign the original SAE Form to confirm agreement with the causality and severity assessments. The form should then be returned to the Trials Office in the post and a copy kept in the ISF.

**9.2.1.3 Provision of follow-up information**

Patients should be followed up until resolution or stabilization of the event. Follow-up information should be provided on a new SAE Form (refer to the SAE Form Completion Guidelines for further information).

**9.2.2 Trials office**

On receipt of an SAE Form seriousness and causality will be determined independently by a Clinical Coordinator. An SAE judged by the Investigator or Clinical Coordinator to have a reasonable causal relationship with the trial medication will be regarded as a Serious Adverse Reaction (SAR). The Clinical Coordinator will also assess all SARs for expectedness. If the event meets the definition of a SAR that is unexpected (i.e. is not defined in the Investigator Brochure) it will be classified as a Suspected Unexpected Serious Adverse Reaction (SUSAR).

**9.2.3 Reporting to the competent authority and main research ethics committee**

**9.2.3.1 Suspected unexpected serious adverse reactions**

The Trials Office will report a minimal data set of all individual events categorized as a fatal or life threatening SUSAR main Research Ethics Committee (REC) within 7 days. Detailed follow-up information will be provided within an additional 8 days.

All other events categorized as SUSARs will be reported within 15 days.

**9.2.3.2 Serious adverse reactions**

The Trials Office will report details of all SARs (including SUSARs) to main REC annually from the date of the Clinical Trial Authorization, in the form of an Annual Safety Report.

**9.2.3.3 Adverse events**

Details of all AEs will be reported to the local authority on request.

**9.2.3.4 Other safety issues identified during the course of the trial**

The local authority and main REC will be notified immediately if a significant safety issue is identified during the course of the trial.

**9.2.4 Investigators**

Details of all SUSARs and any other safety issue which arises during the course of the trial will be reported to Principal Investigators. A copy of any such correspondence should be filed in the ISF.

**9.2.5 Data monitoring committee**

The independent Data Monitoring Committee (DMC) will review all SAEs.

**9.2.6 Manufacturer of advance therapy medicinal product**

All SAEs will be reported to the manufacturer of the Advanced Therapy Investigational Medicinal Product within 24 hours by fax.

**10. Data handling and record keeping**

**10.1 Data collection**

The CRF must be completed, signed/dated and returned to the CORRECT Trial Office by the Investigator or an authorized member of the site research team (as delegated on the Site Signature and Delegation Log) within the timeframe listed below in Table 1. The exception is the SAE Form, which must be co-signed by the Investigator. See AE reporting Section 8.2 for further details.

Table 1: The Case Report Forms (CRFs)

| Case Report Form | Timelines for completion & return to Trial office |
| --- | --- |
| Baseline Assessment Form | Complete prior to treatment |
| Eligibility Checklist | Complete during screening and return immediately following recruitment of the patient |
| Treatment form | Complete the form at the end of each cycle. |
| Follow-up form | Complete after each treatment cycle |
| Adverse Event Monitoring Form | Complete at baseline (i.e. immediately after recruitment) and on completion of each treatment cycle (as per treatment form) |
| Concomitant Medication Form | Complete at baseline (i.e. immediately after recruitment) and on completion of each treatment cycle (as per treatment form) |
| Treatment Discontinuation Form | Complete when the patient finishes treatment regardless of cause |
| SAE Form | Complete the form within 24h of first awareness of the event and fax to the Trials Office immediately (See section 8.2) |
| Relapse Form | Complete immediately upon patient relapse |
| Death Form | Complete immediately upon notification of patient’s death |
| Pregnancy Notification Form | Complete immediately on being notified of patient pregnancy |
| Deviation Form | Complete immediately upon discovering deviation |
| Withdrawal Form | Complete immediately upon patient withdrawal |

Entries on the CRF should be made in ballpoint pen, in blue or black ink, and must be legible. Any errors should be crossed out with a single stroke, the correction inserted and the change initialed and dated. If it is not obvious why a change has been made, an explanation should be written next to the change.

Data reported on each form should be consistent with the source data or the discrepancies should be explained. If information is not known, this must be clearly indicated on the form. All missing and ambiguous data will be queried. All sections are to be completed before returning to the CORRECT Trial Office.

In all cases it remains the responsibility of the Investigator to ensure that the CRF has been completed correctly and that the data are accurate. The completed originals should be sent to the CORRECT Trials Office and a copy filed in the Investigator Site File.

Trial forms may be amended by the Trials Office, as appropriate, throughout the duration of the trial. Whilst this will not constitute a protocol amendment, new versions of the form must be implemented by participating sites immediately on receipt.

**10.2 Archiving**

It is the responsibility of the Principal Investigator to ensure all essential trial documentation and source records (e.g. signed Informed Consent Forms, Investigator Site Files, Pharmacy Files, patients’ hospital notes, copies of CRFs etc.) at their site are securely retained for at least 5 years after the end of the trial. Participating sites will be sent a letter specifying the permissible disposal date. Do not destroy any documents without prior approval from the CTU.

**11. Quality management**

The trial is being managed under the auspices of the CTU according to the current guidelines for GCP and according to their local procedures. Participating sites will be monitored by CTU staff to confirm compliance with the protocol, and the protection of patients’ rights as detailed in the Declaration of Helsinki (Appendix 6).

**11.1 Site set-up and initiation**

All sites will be required to sign a Clinical Study Site Agreement prior to participation. In addition, all participating Investigators will be asked to sign the necessary agreements, CORRECT trial registration forms, and supply a current CV to the Trials Office. All members of the site research team will also be required to sign the Site Signature and Delegation Log, which should be returned to the Trials Office. Prior to commencing recruitment all sites will undergo a process of initiation. Key members of the site research team will be required to attend a meeting covering aspects of the trial design, protocol procedures, Adverse Event reporting, collection and reporting of data and record keeping. Sites will be provided with an Investigator Site File containing essential documentation, instructions, and other documentation required for the conduct of the trial. The Trials Office must be informed immediately of any change in the site research team.

**11.2 On-site monitoring**

Monitoring will be carried out as required following a risk assessment and as documented in the CORRECT Quality Management Plan. Additional on-site monitoring visits may be triggered for example by poor CRF return, poor data quality, low SAE reporting rates, excessive number of patient withdrawals or deviations. If a monitoring visit is required the Trials Office will contact the site to arrange a date for the proposed visit and will provide the site with written confirmation. Investigators will allow the CORRECT trial staff access to source documents as requested.

**11.3 Central monitoring**

Trials staff will be in regular contact with the site research team to check on progress and address any queries that they may have. Trials staff will check incoming Case Report Forms for compliance with the protocol, data consistency, missing data and timing. Where a patient has given explicit consent sites are requested to send in copies of signed Informed Consent Forms for in-house review. Sites will be sent Data Clarification Forms requesting missing data or clarification of inconsistencies or discrepancies.

Sites may be suspended from further recruitment in the event of serious and persistent non-compliance with the protocol and/or GCP, and/or poor recruitment. Any major problems identified during monitoring may be reported to Trial Management Group and the relevant regulatory bodies. This includes reporting serious breaches of GCP and/or the trial protocol to the main Research Ethics Committee (REC).

**11.4 Audit and inspection**

The investigator will permit trial-related monitoring, audits, ethical review, and regulatory inspection(s) at their site, providing direct access to source data/documents.

**12. End of trial definition**

The end of trial will be 6 months after the last data capture. This will allow sufficient time for the completion of protocol procedures, data collection and data input. The Trials Office will notify main REC that the trial has ended and will provide them with a summary of the clinical trial report within 12 months of the end of trial.

**13. Statistical considerations**

**13.1 Definition of endpoints**

See section 2.2-2.4.

**13.2 Analysis populations**

Efficacy will be assessed in all patients who have received at least one dose of camrelizumab and have an adequate baseline tumor assessment.

Safety analysis will be assessed in all patients who have received at least one dose of camrelizumab.

**13.3 Statistical methods**

PFS and OS will be analyzed by the Kaplan-Meier method for all patients, and compared by the log-rank test for different TMB, PD-L1 and microsatellite status subgroups.

Adverse events will be summarized based on frequency and proportion of all patients. The summaries with descriptive statistics will be given for AEs by any toxicity grade, grade 3 or higher AEs, SAEs and AEs leading to discontinuation of study treatment.

**13.4** **Planned interim analysis**

The primary and secondary outcomes will be reported descriptively and presented to an independent DMC annually, along with information relating to trial recruitment and conduct, data completeness, treatment compliance and safety. Analyses that contribute to DMC reports will include no significance testing unless explicitly requested by DMC.

**13.5 Planned final analysis**

The study will complete recruitment within 2 years and the analysis will take place when all patients have been treated and followed-up for at least 1 year.

**13.6 Sample size calculation**

The sample size calculation is based on the primary outcome of PFS. The two-sides Type I error rate is set at 5% and Type II error rate set at 20%, giving 80% power. The accrual period will be 2 years and follow-up period will be 1 year. The 1-year PFS based upon previous study (7), is 20% among unresectable iCCA patients after gemcitabine plus cisplatin therapy. If these patients receive radiotherapy plus anti-PD-1 therapy, the 1-year PFS will be expected to increase to 40%. It is estimated that 36 patients are required allowing for a 10% loss to follow-up/non-adherence rate.

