**5. Study population**

**5.1 Number of patients**

A total of 36 patients will be recruited in the trial. Patients withdrawn from the trial will not be replaced.

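### The 80% power stated in section 13.6 for 36 patients does not carry over to the declared primary endpoint, the 1-year PFS rate, under most fixed-time tests

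*Protocol*

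**What the plan says.** Protocol section 13.6 bases the sample size on PFS. The error rates are given as: "The two-sides Type I error rate is set at 5% and Type II error rate set at 20%, giving 80% power". The reference rate is "The 1-year PFS based upon previous study (7), is 20% among unresectable iCCA patients after gemcitabine plus cisplatin therapy", and the hoped-for rate is 40%. Timing is also stated: "The accrual period will be 2 years and follow-up period will be 1 year". The conclusion is: "It is estimated that 36 patients are required allowing for a 10% loss to follow-up/non-adherence rate". Section 13.6 names neither a formula nor a test.

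Three other places bear on the figure:

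- Section 2.2 and the synopsis make the 1-year PFS rate the primary endpoint. Section 2.2 also censors patients who withdraw or are lost at their last adequate tumour assessment.
- Section 13.3 plans Kaplan-Meier analysis of PFS. The only comparison it names is a log-rank test between biomarker subgroups. It plans no test of the whole PFS curve against a historical one.
- Section 5.1 rules out making up losses: "Patients withdrawn from the trial will not be replaced".

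**The concern.** The stated power should belong to the quantity on which the trial will be judged. Section 13.6 expresses both hypotheses as 1-year rates, and the primary endpoint is a 1-year rate, so a reader takes the 80% as the chance that a true 40% rate is declared better than 20%. A test at a single time point uses less information than a test over all follow-up. A sample size that is adequate for the second can be too small for the first.

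At stake is the chance of missing a true 40% rate. The protocol puts it at one in five. For the usual fixed-time analyses it is nearer one in four to one in three, in a single-arm trial whose efficacy conclusion rests on this one comparison.

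**Working it through.** **Inputs.** From section 13.6: p0 = 0.20, p1 = 0.40, two-sided 5% (z = 1.960), 80% power (z = 0.8416), 2 years of accrual, 1 year of follow-up, 36 enrolled, 10% loss. Evaluable: 36 × 0.9 = 32.4, taken as 32.

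**1. Reproducing the stated 36**

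- *One-sample log-rank test, exponential PFS.* Yearly hazards are −ln 0.2 = 1.609 and −ln 0.4 = 0.916, so the hazard ratio is 0.569. With uniform accrual over 2 years and 1 further year of follow-up, the expected events per patient if the true rate is 40% are 0.817 observed and 0.817/0.569 = 1.434 under the null hazard. The difference is 0.618. The variance terms are 1.434 (null) and 1.842 (alternative). Then n = [1.960·√1.434 + 0.8416·√1.842]² / 0.618² = 31.9, so 32, and 32/0.9 = 35.6, so **36**.
- *One-proportion z-test, null variance in both terms.* n = (1.960 + 0.8416)² × 0.16 / 0.04 = 31.4, so 32, and again **36** after loss.
- *One-proportion z-test, both variances.* n = [1.960·√0.16 + 0.8416·√0.24]² / 0.04 = 35.8, so 36 before loss, and 36/0.9 = **40** after.

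So 36 including loss follows exactly from two calculations. The first uses the accrual and follow-up times that section 13.6 lists, which a one-proportion formula does not need.

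**2. Power for a test of the 1-year rate**

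| Test at two-sided 5% | Patients | Rule | Power at 40% |
|---|---|---|---|
| Normal approximation, both variances | 32 evaluable | – | 76.1% |
| Exact binomial, upper tail at most 2.5% | 32 evaluable | at least 12 (upper tail 1.7%) | 67.7% |
| Exact two-sided (minimum-likelihood) or score test | 32 evaluable | at least 11 (two-sided 4.8%, upper tail 4.1%) | 79.5% |
| The same two tests | 33 evaluable | at least 12 | 72.4% |
| Kaplan-Meier at 1 year, plain Wald | 36 enrolled, 10% censored | – | 67% |
| Kaplan-Meier at 1 year, log-log | 36 enrolled, 10% censored | – | 70% |

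The normal approximation is Φ[(0.2·√32 − 1.960 × 0.4)/√0.24] = Φ(0.709) = 76.1%.

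The Kaplan-Meier rows are from 20,000 simulated trials. They assume exponential PFS and losses spread uniformly over the first year, with lost patients censored as in section 2.2.

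**3. If nobody is lost**

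With all 36 evaluable, the normal approximation gives 80.2%, the equal-tailed exact test 73.8% (at least 13 of 36), and the simulated Kaplan-Meier test about 74%. The equal-tailed exact test first reaches 80% at 41 evaluable and holds it at every size checked from 44.

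**The case against.** The strongest reply is that the stated number is sound for the test it may have been built on. Section 13.6 speaks of PFS and gives accrual and follow-up, which points to a time-to-event calculation, and a one-sample log-rank test returns 36 including loss. Simulated with 36 enrolled and 10% censored, that test has about 85% power. This stands as far as the number goes. It does not rescue the statement of power, because the declared endpoint is the 1-year rate and section 13.3 plans no such test. The log-rank origin is itself an inference, since section 13.6 names no method.

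A second reply is that fixed-time power depends on the test. The rule of at least 11 of 32 is a valid exact two-sided 5% test with 79.5% power, and a Kaplan-Meier test using the null variance simulates at 78%, with an upper-tail error of 3.2%. Both are correct, so it would be wrong to call 67-76% the power under every test. But both reach that power by placing more than 2.5% in the upper tail, and the 79.5% depends on having exactly 32 evaluable.

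A third reply is that the exact form of the test commonly belongs in a statistical analysis plan, which is not at hand. Agreed: the missing test name is not the point. The point is a stated power that most tests of the declared endpoint do not deliver.

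**Conclusion.** The point holds in a limited form. For the 1-year PFS rate at two-sided 5%, 36 enrolled with 10% loss gives about 67-76% power under the usual fixed-time analyses, against the 80% stated. The risk of missing a true 40% rate is then about 24-33%, not 20%. The binomial figures rest on 32 evaluable patients. The Kaplan-Meier figures rest on exponential PFS and losses spread over year 1.

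A reader might infer from the 36-before-loss, 40-after-loss result that the loss allowance was forgotten, or that 36 is an arithmetic slip. The document does not support that. Two other calculations give 32 and then 36 with the allowance applied, and one of them uses the protocol's own accrual and follow-up. What is established is a mismatch between the stated power and the endpoint it is attached to, not an error in the number.

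**What to change.** Keep 36 patients and choose one of two routes in section 13.6.

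- **(a) Keep the 1-year rate as the tested quantity.** Name the fixed-time test and restate its power. Examples at two-sided 5%: with 36 enrolled and 10% censored, a Kaplan-Meier log-log test against 20% has about 70% power at a true 40%; or, with 32 evaluable, at least 12 progression-free at 1 year rejects 20%, with upper-tail error 1.7% and power 68%. If the rule of at least 11 of 32 is preferred, state its attained errors (two-sided 4.8%, upper tail 4.1%), its 79.5% power and its dependence on exactly 32 evaluable.
- **(b) If 36 came from a whole-curve calculation,** say so. Name the one-sample log-rank test of PFS against the historical curve as the primary test in sections 13.3 and 13.6, and specify that curve. Report the 1-year Kaplan-Meier rate with its confidence interval. Under exponential PFS, 36 including loss is adequate for this test.

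The cost is a paragraph or two of text and no extra patients. Under (a) the stated power becomes less favourable. Under (b) the result leans on an assumed historical curve, and that assumption is not trivial. An exponential curve through 20% at 1 year has a median of 12 × ln 2 / 1.609 = 5.2 months, whereas section 1.2 reports a median PFS of 8.0 months for the combination arm of the cited trial, across all biliary tract cancers.
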